## Discussion

Many employees find it hard to disengage from work during non-work time. Research largely found that this is not without costs with respect to well-being. In responding to this salient issue, the paper describes a protocol for a randomized control trial aimed at enhancing psychological detachment from work and employee well-being. More precisely, the article provides a basis for the development and design of a study that enables a direct comparison of the effectiveness of online CBT-based and mindfulness interventions and the assessment of mechanisms of change. Additionally, the paper highlights different factors that are likely to determine the strength of the intervention effects. As such, the study has the potential to extend the knowledge of evidence-based interventions in the workplace context and their refinement. By applying the medical *ex juvantibus* logic (i.e., proposing a diagnosis based on the observed response of the disease to a treatment), the findings of the study will further help to make inferences about the underlying theoretical mechanisms responsible for poor psychological detachment from work and work-related ill-being.

### Strengths and limitations

The proposed study, however, is not without its limitations. First, a more general limitation is related to the focus of the intervention. The intervention can be considered as an individual-focused intervention aimed at teaching employees how to better deal with demanding work conditions and, in turn, become more relaxed and more resilient. As the culture, norms, and practices in many organizations today encourage constant availability and extended work hours [92], some of the underlying causes of poor psychological detachment and ill-being thus will not be tackled. In order to deal with these organizational issues, organization-focused interventions that would result in meaningful changes in the work environment, lower levels of job demands, and increased resources (i.e., job re-design) should also be considered [15]. Moreover, multimodal interventions combining individual- and organization-focused elements should be sought after, as they are most likely to result in sustained beneficial effects for employee well-being [93]. Second, both the CBT and mindfulness interventions are based on a pre-defined set of online exercises and homework, which may undermine the participants’ need for autonomy. Previous studies have shown that workplace interventions should offer participants the opportunity to form their own intervention objectives and exercises during the intervention process [94]. Such a participative design is likely to facilitate intervention effects by being tailored to employees’ specific needs and preferences. Nevertheless, it should be considered that our online interventions provide a high degree of flexibility in terms of time and location of practicing mindfulness and carrying out the CBT exercises and homework. Third, the exercises and homework can take up a significant amount of time. Employees may eventually become less motivated or even fatigued by the added burden to their daily routines, which can attenuate the intervention effects, lead to non-adherence, or even drop-out. Selective drop-out in the CBT intervention group may be particularly problematic, as CBT homework may be perceived as more difficult than mindfulness exercises [33]. The online intervention design can also represent a potential factor of non-adherence and drop-out, as employees may feel less obliged to participate in the protocol than in face-to-face meetings. In line with previous interventions in the workplace context [95], several measures will be taken to avoid these complications. Participants will be briefed about the duration of each of the sessions and the overall intervention in an informed consent form. We will also stress the importance of participating in the study throughout the whole intervention. In-between sessions, participants will also receive e-mail reminders. Adherence will also be monitored by the online platform, which will additionally help to determine whether one of the groups is more compliant with the protocol than the other.

Notwithstanding these limitations, the proposed intervention study is one of the first that is explicitly directed at comparisons between two protocols and mechanisms of change. Both notions are important, as the results may inform theory about psychological detachment and lead to the identification of decisive intervention ingredients. With the focus on work-related maladaptive thinking patterns [40, 84], the work-related well-being literature will potentially gain understanding of a new yet poorly understood, personal vulnerability factor that makes employees more susceptible to ill-being at work or even psychological disorders. Another strength of the intervention is the control of relevant confounding factors. Although the online intervention design may have some drawbacks, the contamination of experimental and control groups will not be a cause for concerns. As participants will not be recruited from one or a small number of organizations and will individually apply for the study, exchanges between participants from different intervention groups are not likely. Given the online protocol, intervention effects also cannot be attributed to positive and supportive interactions between participants [14]. As participants will be blinded to the intervention, the possibility of attenuated or accentuated intervention effects due to participants’ expectations will be minimal. Finally, both online interventions can be utilized by a wide range of professions and can easily be adapted to different workplace contexts and work schedules. The weekly monitoring of effects will further help to customize and shorten similar interventions in the future. As such, the protocol has the potential to significantly advance knowledge about evidence-based CBT and mindfulness interventions and holds promise to be highly applicable to organizational settings.

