### Participants and recruitment

The participants will be recruited from various organizations in Slovenia partnered with the leading institution and through different media channels. The intervention will also be advertised through university newsletters and webpages as well as a well-known Slovenian mental health platform. Interested participants will be able to apply for the study via an online form. Although we will not specifically exclude any professions, employees with knowledge-intensive jobs and high-stress occupations will be primarily targeted [44]. The recruitment stage will begin in August 2020. Following previous intervention studies in the workplace context (e.g., [17, 18]), participants will be pre-screened for eligibility. They will have to meet the following inclusion criteria: 1) being aged 18 or above, 2) working a minimum of 40 h per week and currently not on sick leave, 3) ability to commit (at least) 2 h per week to the online training, 4) ongoing internet connection and computer accessibility, 5) reporting difficulties with psychological detachment from work and burnout at least to a moderate extent. Participants undergoing other forms of treatment (psychotherapy, pharmacotherapy) or who have a clinical diagnosis of mental illness will not be eligible to participate. They will, however, receive additional information on relevant health care services and a link to mindfulness and CBT exercises they can practice on their own. Those eligible to participate will receive detailed information about the intervention and an online informed consent form. Participants who will commit to the study will be randomly assigned to one of the three groups. Following the approach by Querstret and colleagues [17], block randomization based on gender will be used. Participants will be randomized within blocks in such a way that an equal number of females and males are assigned to each of the groups because women exhibit more rumination and difficulties detaching from work at home (e.g., [17]). In order to control for expectations about potential benefits of the interventions, participants will be blinded to the intervention. Both the CBT-based and the MBSR intervention will be advertised as occupational stress-reduction interventions. The participants assigned to the waitlist control group will only be asked to participate in the study and fill out the questionnaires. They will also receive information regarding the delayed starting date of the training.

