#### Intervention design

Both interventions can be classified as low-dose interventions, as they will only last 6 weeks as opposed to more typical 8 weeks programs [26]. However, it has previously been shown that interventions, which are as short as 2 weeks (and are thus more adapted to suit employees with busy work schedules and high workload), can have positive effects on outcomes such as emotional exhaustion [20]. The interventions will combine two types of practice, with each week consisting of two audio-guided active sessions (Mondays and Thursdays; about 30 min each) and home assignments, which will be accompanied by handouts and worksheets (Tuesdays, Wednesdays, Fridays, Saturdays; about 15 min each day).

The first and the last session will serve as an introductory and a closing session, respectively, and will be purely psychoeducational. The main focus of the first session will be on introducing the intervention as well as on increasing the knowledge of core concepts of CBT or mindfulness (i.e., explaining the theoretical framework of the intervention). The last session, on the other hand, will be prepared in such a way that it encourages the participants to continue using the techniques they have learned and that it facilitates the transfer of the newly acquired knowledge into everyday life. In contrast, the central ten sessions will be built around the exercises selected in the preliminary study, ordered in such a way that participants first start with simple and basic exercises and then gradually build upon them (in mindfulness by expanding on the initial experience with the body scan and bringing awareness to the present moment; in CBT by expanding on the initial realization that thoughts are not facts and the ABC model). During the audio-guided session, participants will be taught psychoeducational elements that are specifically relevant for the given exercise and will be guided through their first experience performing the exercise. They will then be encouraged to repeat the exercises on their own in the days that follow, using handouts and worksheets to guide and record their progress. The content of some of the exercises (in both interventions) will be adapted for the working context.

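### The claim that participant blinding makes expectation effects minimal does not hold for the two waitlist comparisons, and holds at most in part for CBT versus MBSR

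*Protocol article*

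**What the plan says.** The claim appears twice. Under *Participants and recruitment* it is given as a design measure with a purpose: "In order to control for expectations about potential benefits of the interventions, participants will be blinded to the intervention". Under *Strengths and limitations* it becomes a conclusion: "As participants will be blinded to the intervention, the possibility of attenuated or accentuated intervention effects" arising from expectations is said to be minimal. Neither sentence is restricted to a particular comparison.

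The procedure behind it is also under *Participants and recruitment*: "Both the CBT-based and the MBSR intervention will be advertised as occupational stress-reduction interventions". For the third arm, the same section says "The participants assigned to the waitlist control group will only be asked to participate in the study and fill out the questionnaires", and then "They will also receive information regarding the delayed starting date of the training".

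Under *Intervention design*, the introductory session of each active program is aimed at introducing the program and at "increasing the knowledge of core concepts of CBT or mindfulness (i.e., explaining the theoretical framework of the intervention".

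According to *Study design* and the measures sections, all constructs are collected by questionnaires that participants fill out themselves. Both primary outcomes (psychological detachment and burnout) are self-report scales.

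**The concern.** Blinding of participants controls expectation effects only if they cannot tell which condition they are in. A common advertising label can hide the fact that two programs are being compared, or which one is favoured. It cannot hide whether someone is being trained or is waiting.

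This matters because objectives (a) and (b) ask whether MBSR and CBT each work, and the hypotheses compare CBT with the control group as well as with MBSR. In the waitlist contrasts, hope in the treated arm and disappointment in the waiting arm can move self-ratings without any specific effect of the training. No outcome comes from a blinded assessor or an objective measure that could offset this. A reader who accepts the stated strength would attribute the whole active-versus-waitlist difference to the program. The limitations discussed in the article cover the individual focus, the fixed set of exercises, and burden and drop-out. They mention neither unblinded waitlist comparisons nor self-report.

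**Working it through.** The claim rests on no figure, so the main check sets the described procedures beside it, contrast by contrast.

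| Contrast | What participants know, as described | Does the claim hold? |
|---|---|---|
| CBT vs waitlist | CBT members are taught the CBT framework in session 1; waitlist members are told of the delayed start | No |
| MBSR vs waitlist | MBSR members are taught the mindfulness framework in session 1; waitlist members are told of the delayed start | No |
| CBT vs MBSR | Each side knows its own content; both saw the same neutral label | At most in part |

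1. *Waitlist.* Members told that training will start later, and asked meanwhile only for questionnaires, know they are untreated, at least up to the post-intervention assessment (T2).
2. *Active arms.* Members know they are being trained, and from session 1 which framework they are being trained in. The article does not say that they learn about the other program or the superiority hypothesis, so the neutral label may still do some work between these two arms.
3. *Outcomes.* All are self-rated, so the point applies to every outcome in the two waitlist contrasts.

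**The plan's own figure.** The sample size does not depend on this point, but it was checked. For the time-by-group interaction in a repeated-measures MANOVA with 3 groups and 3 times: s = 2, df1 = 4, df2 = 2(N − 3), noncentrality λ = 2 × N × 0.25² = 0.125N, α = .05.
- N = 151: λ = 18.875, df2 = 296, power 0.9500 (stated .95).
- N = 98: λ = 12.25, df2 = 190, power 0.8005 (stated .80).

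Both stated sizes reproduce.

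**Illustration on assumed values.** The documents give no size for an expectation effect. Assume no true effect and a pure expectation shift of δ standard deviations between an active arm and waitlist, tested by a simple two-sided two-group comparison with n per group. The chance of a significant result is

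P = 1 − Φ(c − δ/√(2/n)) + Φ(−c − δ/√(2/n)),

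where c is the two-sided critical value. For n = 50, δ = 0.2 and α = .05: √(2/50) = 0.20, δ/0.20 = 1.0, and P = 1 − Φ(0.96) + Φ(−2.96) = 0.170.

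| Assumed δ | n = 50, α = .05 | n = 50, α = .05/3 | n = 33, α = .05 | n = 33, α = .05/3 |
|---|---|---|---|---|
| 0.1 | 7.9% | 3.1% | 6.9% | 2.6% |
| 0.2 | 17.0% | 8.2% | 12.8% | 5.8% |
| 0.3 | 32.3% | 18.6% | 23.0% | 12.0% |
| 0.4 | 51.6% | 34.7% | 36.9% | 22.1% |

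Without a shift the rates would be 5% and 1.7%. The group sizes are the approximate ones under *Sample size calculation*. Dividing α by 3 assumes a Bonferroni correction over three pairwise comparisons. This is not the planned time-by-group ANOVA, and the table does not estimate the trial's bias. It shows only that whether the effect is minimal depends on a quantity the article neither gives nor bounds.

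**The case against.** The strongest defence is that blinding was meant narrowly. In the recruitment section the blinding sentence is followed at once by the common label for CBT and MBSR, and the waitlist is then described separately and openly. The paragraph in the Discussion opens on the comparison of two protocols. On this reading, participants are masked to which type of program was advertised and which is favoured, and session 1 reveals only their own framework. The article says of the pre-enrolment material only that "Those eligible to participate will receive detailed information about the intervention and an online informed consent form", so what was disclosed about the arms cannot be seen. This has force for CBT versus MBSR, and it is why the claim is called partial there and not false. It does not rescue the waitlist contrasts, because neither sentence is limited to the active arms and the Discussion draws a general conclusion about intervention effects.

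It is also fair that an open waitlist control and self-rated outcomes are disclosed, legitimate choices. The fault lies in the claim made about them.

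Four stronger readings are tempting, but the documents do not support them:
- *That waitlist members learn their group before the baseline assessment (T1).* The article puts assignment after commitment and T1 just before the intervention, but never says when allocation is disclosed.
- *That an allocation-aware T1 would carry the same bias into change scores.* If disappointment worsens waitlist scores by d1 at T1 and d2 at T2, the bias in the change contrast is d2 − d1. Equal shifts cancel, and a shift at T1 alone works against the intervention.
- *That the protocol says expectation effects are excluded.* Its word is minimal.
- *That CBT versus MBSR controls for expectations.* Participants know their own program, so equal expectancy is not established.

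**Conclusion.** The statement is wrong as written for two of the three pairwise contrasts, on every outcome, and at most partly true for the third. This follows from the article's own description of the waitlist, session 1 and the measures, and needs no outside assumption. The size of any expectation effect is unknown; the tabulated rates rest on assumed shifts and should not be quoted as its magnitude.

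The consequence is limited to interpretation. A difference from waitlist, under objectives (a) or (b), may combine a program effect with expectation or disappointment, and the article should not tell readers that this has been controlled. Randomization, sample size and the planned models are untouched. The correction should be made because it is specific and almost free.

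**What to change.** In *Participants and recruitment* and in *Strengths and limitations*, replace the statements that participants are blinded and that expectation effects are minimal. Suggested text: *Both active programs carry the same neutral label, which may help to balance expectations between CBT and MBSR. Participants know the content of their own program, and waitlist participants know that they are untreated.*

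Add to the limitations: *The comparisons of CBT and of MBSR with the waitlist use self-rated outcomes without blinding and may include expectation or disappointment effects.* Interpret objectives (a) and (b) accordingly in the results report.

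As an optional safeguard, confirm that T1 is completed before allocation is disclosed, and state the order. If an expectancy rating is considered, its timing needs care: weekly questionnaires are filled out before the new exercise, so one in week 1 could precede the session that explains the program.

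The cost is a few sentences and a weaker claim for the two waitlist comparisons. No change to sample size or analysis is needed.

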## Data Availability

Anonymized raw data will be shared with researchers upon request by contacting the corresponding author (after completion of the research project).

## Abbreviations

CBT: Cognitive-Behavioral Therapy
MBSR: Mindfulness-Based Stress Reduction
MBCT: Mindfulness-Based Cognitive Therapy
CONSORT: Consolidated Standards of Reporting Trials
PSQI: Pittsburgh Sleep Quality Index
WIF: Work Interference With Family
PA: Positive Affect
NA: Negative Affect
DASS-21: The Depression, Anxiety and Stress Scale - 21
MAAS: The Mindfulness Attention and Awareness Scale
ISTA: Instrument for Stress-Related Job Analysis
MANOVA: Multivariate Analysis of Variance
ANOVA: Analysis of Variance
